### 2.6. Sample size and data analysis

Although sample size calculations are not necessary for observational registry studies, we have determined that 420 individuals are needed, considering the volume of business at the outpatient clinics taking part in this study.

Each outcome measure will be compared to the clinical outcome between the baseline and termination, and the clinical outcome will be a dependent variable. Combinations of the applied acupoints will act as independent factors to predict the most effective acupoints for the acupuncture treatment. To improve the effectiveness of acupuncture treatments for FGID patients, the properties of the acupoints will be extracted using machine learning algorithms, such as support vector machine and logistic regression models.

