Next, the best acupoints for treating FGID with acupuncture will be predicted using machine learning and the patient results. Individuals respond to acupuncture in different ways.^[18]^ As mentioned above, machine learning can be used to forecast the best acupoints based on patient outcomes. In a previous study, the effectiveness of acupuncture was predicted using a support vector machine for individuals with FD.^[11]^ Gender, disease subtype, and education level were significant predictors of treatment results. Similarly, machine learning will be used to identify those who are more likely to respond to acupuncture, or those who will improve (display minimally clinically significant differences) from baseline following 4 weeks of acupuncture treatment. Data from 80% of the patients with FD will be used to create a predictive model, and the data from the other 20% will be used to validate the model and assess its performance. The performance of supervised machine learning models, such as support vector machine and logistic regression models, will be assessed using accuracy, sensitivity, and specificity analyses. Machine learning can be used to predict the optimal acupoints for each patient and help doctors assess treatment responses.

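### The three named performance measures all need a yes/no cut, so they discard ranking information in a small held-out set; adding the AUC and a larger-class benchmark is a cheap improvement

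*Protocol article*

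**What the plan says.** The Discussion describes the prediction task. The outcome is a yes/no responder status, identifying "those who will improve (display minimally clinically significant differences) from baseline following 4 weeks of acupuncture treatment". Four fifths of the FD patients serve to build the model, while "the data from the other 20% will be used to validate the model and assess its performance". The measures are then named: for model types that include logistic regression and the support vector machine, performance "will be assessed using accuracy, sensitivity, and specificity analyses". The paragraph closes with a remark on use: "Machine learning can be used to predict the optimal acupoints for each patient and help doctors assess treatment responses".

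Section 2.6 names the same two model types and gives the sample size on practical grounds: "we have determined that 420 individuals are needed, considering the volume of business at the outpatient clinics taking part in this study". It adds no performance measure. The article gives no rank-based measure, calibration measure, larger-class benchmark, classification cut-off or expected responder share.

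**The concern.** The article makes a positive choice of three measures, and all three require each patient's score to be cut to yes or no. Two things follow.

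- **Ranking is lost.** Two patients on the same side of the cut count the same, however far apart their scores are. In a held-out set of 84 or fewer, that loss matters for whether real predictive ability can be seen.
- **Accuracy has no fixed reference point.** Calling everyone a member of the larger class already scores that class's share. An accuracy of 72% is a clear success if half the patients respond, and almost nothing if 70% do.

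A model that ranks patients moderately well could therefore look close to uninformative, and an accuracy figure could look good only because most patients respond.

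**Working it through.** **Figure to reproduce.** None. The article states no performance target, responder share or power.

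**Inputs from the article.** Planned enrolment is 420 (sections 2.2 and 2.6). The split is 80/20 among FD patients (Discussion). The held-out set is at most 0.20 × 420 = 84. It will be smaller, because section 2.3.1 also admits irritable bowel syndrome and the FD share is not given.

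**Assumptions, not in the article.** The model score is normal with equal variance in responders and non-responders. The true AUC is 0.70. The responder share p is 50% or 70%. Tests are one-sided at 2.5%.

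**Step 1: separation.** d = √2 × z(0.70) = 1.414 × 0.524 = 0.742.

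**Step 2: what the three measures show.** With cut-off t, sensitivity = Φ(d − t), specificity = Φ(t), and accuracy = p × sensitivity + (1 − p) × specificity. The accuracy-optimal cut-off (predicted probability 0.5) is t = d/2 − ln(p/(1 − p))/d. The balanced cut-off is t = d/2.

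For p = 0.70, the accuracy-optimal t = 0.371 − 0.847/0.742 = −0.77. Sensitivity is Φ(1.51) = 0.935 and specificity is Φ(−0.77) = 0.220. Accuracy is 0.70 × 0.935 + 0.30 × 0.220 = 0.720.

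| Responder share | Cut-off | Sensitivity | Specificity | Accuracy | Larger-class share |
|---|---|---|---|---|---|
| 50% | either (they coincide) | 0.645 | 0.645 | 0.645 | 0.500 |
| 60% | accuracy-optimal | 0.821 | 0.430 | 0.664 | 0.600 |
| 70% | accuracy-optimal | 0.935 | 0.220 | 0.720 | 0.700 |
| 70% | balanced | 0.645 | 0.645 | 0.645 | 0.700 |
| 80% | accuracy-optimal | 0.987 | 0.067 | 0.803 | 0.800 |

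The AUC is 0.70 in every row. At a 70% share the same model has an accuracy 2 points above calling everyone a responder, or 5.5 points below it, depending only on the cut-off. With 84 patients, the 95% half-width of an accuracy near 0.75 is 1.96 × √(0.75 × 0.25/84) = 0.093, so a 2-point gain cannot be seen.

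**Step 3: how much information the cut costs.** Simulated chance of showing better-than-chance prediction (Mann–Whitney test for the AUC, Fisher test for the 2x2 table, binomial test of accuracy against the larger-class share; several thousand runs):

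| Held-out n, responder share | AUC | 2x2 table, accuracy-optimal cut-off | 2x2 table, balanced cut-off | Accuracy (accuracy-optimal cut-off) |
|---|---|---|---|---|
| 84, 50% | about 91% | about 70% | same cut-off | about 74% |
| 84, 70% | about 84–85% | about 39% | about 60% | about 4–5% |
| 42, 70% | about 52–54% | about 15% | not tabulated | about 3% |

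At a 50% share the choice between these two cut-offs does not arise, so the gap of about 21 points there comes from dichotomising alone, together with the conservatism of the Fisher test.

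**Step 4: calibration.** Multiplying the model's logit by 3 (simulated at a 50% share) leaves accuracy (0.645), sensitivity (0.646) and specificity (0.645) unchanged. The mean prediction in the top tenth of patients rises from 0.80 to 0.98, against 0.79 observed. The Brier score moves from 0.219 to 0.249. The three named measures do not respond to this kind of error.

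**The case against.** **It is one sentence in a condensed article.** It lists three conventional measures, and an analysis plan that is not shown may add others or set the cut-off. This limits the weight of the point. It does not remove it, because the sentence states which measures will be used, and the criticism is of that choice.

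**The size depends on an assumed cut-off and test.** This largely stands. A balanced cut-off lifts the 2x2 table from about 39% to 60% at a 70% share. Replacing the Fisher test with the two-proportion z-test gives about 70% there, and about 78% at a 50% share. The AUC remains ahead, at about 85% and 91%. At a 60/40 split, imbalance does little harm to sensitivity and specificity.

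**No test of performance and no accept-or-drop rule is planned.** This stands. The percentages show relative information and are not the power of any planned analysis. Sensitivity and specificity reported together would also reveal a lopsided cut-off.

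**Stronger readings that a reader might infer.** One is that the plan judges models at a single fixed cut-off. The article states no cut-off, so this is not supported. The other is that the closing remark, "Machine learning can be used to predict the optimal acupoints for each patient", commits the study to comparing predicted probabilities, and that an AUC or calibration check would validate that choice. The article does not say how acupoints would be compared. Any measure computed across patients on the acupoints they actually received leaves the choice among acupoints for one patient untested. The logit example in the working also preserves every ranking, so it would change no choice made by rank.

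**Calibration is imprecise at this size.** This stands. For a perfectly calibrated model, the estimated slope ranged from 0.35 to 1.90 (2.5th to 97.5th percentile) with 84 patients and from 0.06 to 2.55 with 42.

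**Conclusion.** The point holds as an efficiency and interpretation problem. The three named measures use only a yes/no version of the score, and accuracy is uninterpretable without the larger-class share. With a true AUC of 0.70 and 84 held-out patients, the chance of showing prediction better than chance falls from about 84–85% with the AUC to about 39–60% with the 2x2 table at a 70% responder share, and from about 91% to 70% at a 50% share. The responder share, the AUC, the score distribution, the cut-offs and the tests are all assumptions. Only the bound of 84 and the three measures come from the article. The point is of low to moderate importance: the measures are conventional and the analysis is exploratory, but a better main measure is available from the same data.

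**What to change.** In the performance sentence of the Discussion, and in any analysis plan:

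- Make the AUC with its 95% interval the main measure in the held-out patients. Logistic regression supplies predicted probabilities and the support vector machine supplies decision values, so both can be ranked.
- Report accuracy beside the share of the larger class.
- Give sensitivity and specificity at a cut-off fixed in the 80% training data, before the held-out data are examined.
- Optionally add the Brier score and the calibration intercept and slope as descriptive results, noting that they will be imprecise at this size. For the support vector machine this needs a scaling of its decision values to probabilities, fitted in the training data.

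The revised sentence should not present these measures as validating the choice of acupoints for an individual patient. The cost is a sentence or two of text and a few lines of analysis, with no new data and no additional participants.
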